# Case Method in COPD education for primary care physicians: study protocol for a cluster randomised controlled trial

**DOI:** 10.1186/s13063-017-1889-4

**Published:** 2017-04-27

**Keywords:** Case methodology, Continuous medical education, Professional training, Primary care physicians, COPD, Primary care, Cluster randomised controlled trial

## Abstract

**Background:**

Chronic obstructive pulmonary disease (COPD) is a common cause of morbidity and mortality worldwide. It is often undiagnosed and insufficiently managed. Effective forms of continuing medical education (CME) for primary care physicians (PCPs) are necessary to ensure the implementation of guidelines in clinical practice and, thus, improve patients’ health.

**Methods:**

In this study, we will measure the effects of CME by Case Method and compare them against those of traditional lectures and no CME at all through an unblinded, cluster randomised controlled trial (CRCT). Thirty-three primary health care centres (PHCCs) in Stockholm, Sweden, with a total of 180 PCPs will be involved. Twenty-two primary PHCCs, will be cluster-randomised into: an intervention group who will receive CME by Case Method (*n* = 11) and a control group who will receive traditional lectures (*n* = 11). The remaining PHCCs (*n* = 11) will be a reference group and will receive no CME. From the intervention and control groups, 460 randomly selected patients with COPD in GOLD stages 2 and 3 will participate, while no patients will be recruited from the reference group.

For the patients, smoking status, actual treatment and urgent visits to a health provider due to airway problems will be registered. For the PCPs, professional competence (i.e. knowledge and management skills) in COPD, will be measured using a questionnaire based on current guidelines and guideline implementation problems in clinical practice which has previously been described by the authors. Data will be collected at baseline and at follow-up, which will be after 1.5 years for the patients, and 1 year for the PCPs.

Statistical methods for individual-level and cluster-level analyses will be used.

**Discussion:**

COPD is considered a particularly complex clinical challenge involving managing multimorbidity, symptom adaptation, and lifestyle problematisation. Case Method in CME for PCPs may contribute to a better understanding of the impact of COPD on patients’ lives and, thus, improve their management of it. The present study is expected to contribute scientific knowledge about indicators for an effective CME in COPD that is tailor-made to primary care physicians.

**Trial registration:**

ClinicalTrials.gov, identifier: NCT02213809. Registered on 10 August 2014.

Protocol version: Issue date: May 2014.

**Electronic supplementary material:**

The online version of this article (doi:10.1186/s13063-017-1889-4) contains supplementary material, which is available to authorized users.

Case Method can be used to create an interactive type of CME for a particular area of interest or a specific problem based on the professionals’ perspective. [11]. According to an earlier Swedish study, use of case-based training for implementing evidence-based practice in primary care was associated with decreased mortality in patients with coronary heart disease [12]. In addition, an American study showed a 50% increase in evidence-based treatment and management of COPD among PCPs who received case-based CME compared with colleagues who did not [13]. However, the effectiveness of interactive CME in COPD carried out at medical centres, or primary health care centres (PHCCs), with both physicians and patients as endpoints, has not been previously studied. We believe that a cluster randomised trial that uses the PHCC as a randomisation and analysis unit would be a suitable study design as it takes into account the effect of CME reaching all PCP staff of a PHCC at once.

### Objective and hypothesis

The overall objectives of this randomised controlled trial pertain to individual patients and PCPs. The effectiveness of Case Method in COPD CME for PCPs will be evaluated and compared to that of traditional lectures as well as lack thereof. The main aim is to evaluate and compare the effects of CME on physicians’ competence with regard to the COPD care that patients will receive. The primary outcome measure is the difference in the mean total score on *The Clinical COPD Questionnaire* (CCQ) [14], a validated tool to evaluate disease-specific health status in patients with COPD. Secondary outcome measures include the difference in the total score on *The COPD Assessment Test* (CAT), another validated disease-specific questionnaire measuring health status [15] and in *The Lung Information Needs Questionnaire* (LINQ), which measures patient’s satisfaction in COPD care and information received [16]. At the same time, changes in COPD medication and participation in pulmonary rehabilitation, number of exacerbations, and smoking habits will be recorded.

Apart from evaluating effects, a description of the participating PHCCs will be performed focussing on the organisation of COPD care that they offer to their patients; for example, whether they have a nurse-led COPD clinic in the PHCC or not.

Our hypothesis is that CME for PCPs that is based on Case Method is more effective than traditional lectures or no CME at all in improving the disease-specific health status of COPD patients, due to physicians’ improved knowledge and skills in COPD management.

## Methods and design

This paper was written in line with the SPIRIT (Standard Protocol Items: Recommendations for Interventional Trials) 2013 explanation and elaboration: guidance for protocols of clinical trials [17], and the CONSORT (Consolidated Standards of Reporting Trials) 2010 Statement: extension to cluster randomised trials [18]. The SPIRIT Checklist and flow chart were used, see Additional file 1 and Fig. 2.

### Study design

This study involves a pragmatic and unblinded cluster randomised controlled trial (CRCT) with PHCCs as units of randomisation. In order to isolate the effect of CME, by Case Method, three groups (arms) will be established: one where CME by Case Method will be offered (arm 1, 11 PHCCs), one where traditional lectures (arm 2, 11 PHCCs) will be offered, and one where no CME will be offered at all (arm 3, 11 PHCCs). There will be a total of 33 PHCCs, or 33 clusters, from Stockholm County. From these, 180 PCPs (60 PCPs for each arm) and 460 patients (230 for arms 1 and 2, no patients for arm 3) will be asked to participate. Each PHCC will provide 25–30 patients, which will yield the minimum of 460 patients with COPD in GOLD stages 2 or 3 [2]. The outcome measures will be recorded at baseline and at follow-up which will be after 1 year for PCPs and 1.5 years for patients. The trial design is summarised in Fig. 1 and Fig. 2 as flow charts.

**Fig. 1 Fig1:**
[figure not shown]
Flow chart of the trial

**Fig. 2 Fig2:**
[figure not shown]
Enrolment, interventions and assessments according to Standard Protocol Items: Recommendations for Interventional Trials (SPIRIT)

### Participants

#### Eligibility

The study will include 33 PHCCs (clusters) in Stockholm County with more than 10,000 registered patients in each PHCC. Patients with COPD at stages 2 or 3 according to the GOLD criteria [2] who will be willing to participate will be included in the trial. Within each cluster, the participating PCPs will have acquired specialist training in family medicine with a minimum of 5 years of completed or ongoing training, according to the requirements by the National Board of Health and Welfare in Sweden http://www.socialstyrelsen.se/english/Documents/Doctors-specialist-medical-training-National-Board-of-Health-and-Welfare.pdf. To minimise the dropout risk due to short-term employments, temporary PCPs working or training at a PHCC will be excluded, though, by attending CME sessions, they may have an impact on study outcomes.

#### Recruitment of PHCCs and participants

##### Recruitment of the PHCCs

In Sweden, almost all PCPs are employed by PHCCs, which are medical centres run by county councils directly or by contracted private companies. According to the policies of county councils, all PHCCs must provide the general population with certain primary care services that are carried out by PCPs and district nurses. In practice, all COPD patients in GOLD stages 2 and 3, and many in stage 4, are identified, examined and managed entirely in primary care. Primary care rehabilitation units in Stockholm County are often independently organised and managed separately from PHCCs.

Managers and PCPs of all 80 medium-sized or larger PHCCs (defined as caring for more than 10,000 registered patients, typically yielding five to ten eligible physicians per PHCC), which represent 40% of all 205 PHCCs in Stockholm County, will be contacted by a letter (by post and e-mail) which will serve as an invitation to participate in the study. To meet the required number of patients determined by the power calculation, a minimum of 11 PHCCs per arm will be needed. The number of PHCC depends on access to spirometry results, since a spirometry-verified COPD diagnosis is needed for inclusion. In Stockholm County primary care, there are currently technical and patient confidentiality issues that prevent the collection of data from digitally shared medical records, thus limiting access to spirometry results. Socioeconomic and demographic factors as well as characteristics of the PHCC, such as staffing and access to a nurse-based asthma/COPD clinic within the PHCC, will be taken into consideration during the data analysis and appropriate adjustments will be made for these factors in the models. Signed Informed Consent Forms will be obtained from all PCPs and managers who agree to participate. The first 22 PHCCs signing up will be included in the study and randomised into one of the two interventions arms. The remaining PHCCs with more than 10,000 registered patients will be contacted and the first 11 that accept participation will form a reference group. These PHCCs will not receive a CME, which makes randomisation into a reference arm difficult to motivate ethically.

##### Recruitment of PCPs and data collection

PCPs will be recruited for all three study arms. After agreeing to participate, the manager of the PHCC will receive oral and written information about the study during a face-to-face meeting with the research project manager. The manager of the PHCC then will inform the PCPs that participation in the study will be optional. The PCPs who attend the CME sessions will then, again, be contacted and informed by the CME leader prior to collecting baseline data at the beginning of the first CME session. The reference group will be informed by their manager and by a researcher who will collect baseline data at a specific occasion at each PHCC. By taking the expected response (90%) and dropout rate (20%) into account at the end, the 33 PHCCs will be expected to engage approximately 180 eligible PCPs (60 per arm) whose signed Informed Consent Forms will be required. The PCPs will be informed of their right to withdraw from the study at any time without negative consequences.

The completed questionnaires will be collected by the research group and be put in an envelope and stored in a secure place. The endline data will be collected 1 year after a completed CME during a follow-up visit at each PHCC. The persons who will be absent will be contacted separately to collect their individual endline data.

##### Recruitment of patients and data collection

Patients will be recruited only for arms 1 and 2, i.e. the intervention and control groups. A total of 990 randomly selected patients with COPD in GOLD stages 2 and 3 [2] (495 in each arm, 40–50 randomly selected eligible patients per PHCC unit) will be invited to participate. With an expected response rate of 60% at baseline and 80% at endline, a total of 230 patients per arm will be included. To ensure the eligibility of the patients, a spirometry slip together with an *International Classification of Diseases, version 10* (ICD-10) diagnosis of COPD (J44.0–J44.9) in the PHCC’s medical records, will be included and reviewed by the research group. Patients with a diagnosis of COPD in the records, but who do not fulfil the criterion of a FEV_1_/FVC ratio <0.7, will be excluded. An independent person, such as a nurse or an administrator, will handle the patient codes for maintaining their anonymity as well as send out the invitation letters. Together with the invitation letter, the patients will receive information about the study, an Informed Consent Form to fill in and the questionnaire (Additional file 2) in a self-addressed envelope to return to the researchers. Two reminder letters will be sent to the patients who have not replied at 2 weeks apart. The patients will be informed that they can withdraw from the study at any time without negative consequences. After receiving the informed consent from the patient, the coding key will be handed over to the researchers. The patient recruitment period will last for 2 months prior to the CME intervention at each PHCC. The endline data will be collected by mail (including two reminders) 1.5 years after the PCPs have completed the CME.

Due to the relatively small-scale collection of data, a Data Monitoring Committee is not deemed necessary.

### Interventions

#### The CME programmes

The CME sessions will take place at the PHCCs. The five CME leaders with strong competence in COPD management and experience/training in Case Method when required, will run two 120-min sessions at each PHCC, at a maximum of 3 months apart. Each PHCC will be assigned the same CME leader, but only one of these two approaches will be used. Each leader will abide by the well-defined intended learning outcomes (ILOs) and contents of the CME (Table 1) but will be allowed to use different presentation materials, such as slide shows and handouts.

**Table 1 Tab1:**
[figure not shown]
A summary of how the Constructive Alignment links the SOLO^a^ levels, ILOs^b^, teaching/learning methods and examination questions

^a^SOLO = Structure of Observed Learning Outcome taxonomy

^b^ILOs = intended learning outcomes

#### Patient-doctor consultations – care as usual

No interventions for patients will take place. Patients will visit their PHCC as usual during the study time.

#### Relevant parallel, permitted interventions

As new guidelines for COPD care in Sweden are expected to be published during the study period, the participating PCPs will not be asked to decline participation in other eventual COPD educational occasions during the study period. In any case, the PCPs will be likely recipients of information about updated COPD guidelines through different channels.

#### Description of CME by Case Method (intervention group, arm1)

After an initial 20-min introduction to the topic via a traditional lecture, the CME leader will start presenting a case seminar. The reason behind using cases lies in having students acquaint themselves with realistic problems or ‘cases’ with authentic, open-ended narratives out of realistic situations [19]. The cases will be read discussed at a seminar at each PHCC with 5–15 eligible PCPs. The two cases – one for each seminar – are described in Additional files 3 and 4. The emerging questions in a case have typically no obvious right or wrong answer – instead they can be answered in several acceptable ways. The CME leader will act more like a facilitator rather than an expert, encouraging the participants to try and solve problems through detailed discussions, reflection and collaboration, based on the knowledge, skills, and experiences that they already possess. Thus, the CME leaders will not always have clear-cut answers to possible questions from the participants – instead the questions will be up to the participants to answer. The primary aim is to improve decision-making skills in clinical practice. The learning outcome of a case seminar will largely depend on the participants’ level of activity and the facilitator’s ability to encourage the discussion in an open, respectful, and creative educational setting.

#### Description of sessions using traditional lectures (control group, arm 2)

Traditional lectures are lectures delivered in a didactic style, with the CME leader acting as an academic expert, i.e. they will decide on the content of the session and will teach by mainly one-way communication using slide show presentations as a pedagogical tool. Some interaction between the leaders and the students will occur, such as answering questions put forward by the students.

#### Intended learning outcomes (ILOs) of the CME

When designing the CME sessions, we will follow the Bologna Declaration [20]. We will start with the intended learning outcomes (ILOSs), and will then adjust teaching style and assessment method to fit those learning outcomes. This principle is an example of an outcome-based education and it is known as Bigg’s Constructive Alignment [21]. It is an influential educational theory that merges constructivism with alignment, i.e. the idea that ILOs, teaching and learning activities, assessments, and examination questions should work together (be aligned) to enable learners to achieve deeper levels of knowledge. Bigg’s Structure of Observed Learning Outcomes (SOLO) taxonomy [22] helps to map levels of understanding that can be built into the ILOs. SOLO levels 1–3 (S1 = prestructural, S2 = unistructural, S3 = multistructural) are typically integrated into the PCPs’ basic education, i.e. medical school. Levels 4–5 (S4 = relational, S5 = extended abstract) involve gradually increasing demands on reflection, hypothesising, creativity, discussion, and abstraction so that the learners can apply the new skills to new and broader areas [21, 23].

A summary of how the Constructive Alignment links the ILOs, teaching/learning methods and examination questions in our CME in COPD is shown in Table 1.

The intervention group (arm 1, CME by Case Method) will receive CME at SOLO levels 1–5 (S1–S5), with more focus on levels S3–S5, whereas the control group (arm 2, traditional lectures) will receive CME only at S1–S3. The contents of the ILOs are based on current evidence-based COPD guidelines [2, 24–26] and problem areas in managing COPD, as described in a previous study by the authors [27]. After analysing interviews with PCPs, the aforementioned study revealed problem areas from real-life primary care settings closely connected to time constraints during patient-doctor consultations that often lead to deprioritising of COPD. The examination questions will be based on ILOs emerging from S1–S3, hence covering both groups.

### Outcome parameters and planned statistical methods

Outcomes are chosen for their ability to assess the effect of the interventions on both patient and PCP individually as well as on PHCCs as a whole (cluster). For data collection, validated questionnaires together with study-specific questions will be used. The baseline data collection will be completed prior the first CME session for the PCPs. Endline data for PCPs and patients will be collected 1 year and 1.5 years, respectively, after a completed CME.

The primary outcome of the study will be the effect of CME on patients’ disease-specific health status. Hence, the power calculations for the study have been performed on the basis of the primary outcome measure for patients rather than PCPs.

#### Primary outcome measures for patients

A patient questionnaire (Additional file 2) consisting of three validated self-report instruments and study-specific questions will be used. The primary outcome measure will be the mean total score in *The Clinical COPD Questionnaire* (CCQ) which is a validated, self-administered questionnaire specifically developed to measure clinical control in patients with COPD [14]. It consists of 10 items, divided into three domains: symptoms, functional state, and mental state (scale per each item: 0 = best, 6 = worst). The higher the score, the greater the negative impact on quality of life and health status. The final measure is the mean value of the 10 questions; Minimal Clinically Important Difference = 0.44 of the final score (mean value) [28]. We will adjust for CCQ at baseline and the CCQs with the minimum of 6 of 10 items replied will be included in the analysis. The CCQ is constructed as an ordinal scale, and the statistics will be analysed accordingly. However, since the CCQ, as most symptom scales, is practically an interval scale, we will present the results using the mean instead of the median, to be able to compare our observations with those of earlier studies [29, 30].

#### Secondary outcome measures for patients

*The COPD Assessment Test (*CAT) will be used to access the impact of COPD on health status [15]. It consists of eight items covering coughing, phlegm in chest, chest tightness, breathlessness on exertion, limitations to doing activities at home, being confident leaving home, ability to sleep soundly, and feeling energetic. The scoring scale ranges between 0 and 5 for each item, and the total score ranges from 0 to 40. The higher the score, the greater the impact of COPD is on the patient’s health; Minimal Clinically Important Difference = 2 [31].

*The Lung Information Needs Questionnaire* (LINQ) will be used to assess the patient’s need for education and support in self-managing COPD, and their level of satisfaction with received COPD care. The questionnaire consists of 20 items that are divided into six categories: disease knowledge, medicine, self-management, smoking, exercise and diet [16]. The scoring scale ranges from 0 to 1, 0 to 2 or 0 to 3 for each item, and the total score ranges from 0 to 25. The higher the score, the greater the learning need; Minimal Clinically Important Difference = 1 [32].

Additional self-reported information on age, weight, length, educational level, tobacco use, and hospitalisations due to airway problems will be collected.

#### Outcome measures for PCPs

The outcome measures for the PCPs pertain to individual participants. The Physician Questionnaire (Additional file 5) has been constructed by the researchers. The questionnaire is in fact an outright examination in line with the Constructive Alignment: the items cover the ILOs of S1–S3, leaving out the ILOs of S4–S5, as the latter ones will only be applicable for the intervention group, as shown in Table 1. The questionnaire is designed as an assessment test consisting of five short patient cases, with two to three questions per case (13 in total). The questions touch upon ‘knowledge/skills’ and ‘practical management’ yielding 0–2 points each, and appear as either:
*Multiple choice questions.* These questions mainly cover the areas of ‘knowledge/skills’, based on the ILOs concerning the current guidelines for COPD care. For instance, interpreting a spirometry result will be tested by a multiple choice question, implying one correct answer out of seven options. However, for questions such as on correct treatment of COPD exacerbation, several options can be ticked. A correct answer gives 2 points, partially correct 1 point, and all other replies result in 0 points
*Open Questions.* These questions are based on the ILOs related to specific realistic problems in COPD management encountered in primary care, which have been described in a previous study by the author that was based on interviews with PCPs [27]. These problems are often faced in everyday practice and can be caused by deprioritising of COPD due to time pressure during a doctor-patient consultation. Open questions address issues such as ‘not becoming concerned due to clinical features’, ‘insufficient local routines for COPD care’, ‘negative personal attitudes and views about COPD’, ‘not managing COPD due to multimorbidity,’ and ‘perceiving a patient’s motivation as low’. For instance, two open questions address PCPs’ support of patients who try to quit smoking and provide PCPs with a possibility to state personal opinions and values or to describe own COPD management routines. Notably, each reply is considered correct only when it is in line with current COPD care guidelines, regardless of personal views on the subject. The free text replies will be analysed by quantitative content analysis, yielding 0–2 points according to a correction template, which will be constructed in alignment with the guidelines.Also, at baseline, PCPs’ characteristics, such as sex, age, and years in the profession, will be registered for use in the analysis and descriptions of responders and nonresponders.

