### PCPs

The nature of the intervention, where the participants in arms 1 and 2 will be offered a CME whereas the reference group will not, may imply difficulties in recruiting reference participants. This affects our decision to recruit the reference group separately. The reason for the inclusion of a reference group is to assess a possible effect of general information on COPD that PHCs might receive as the national guidelines are to be revised during the study period. Also, despite mutual ILOs for the different types of CME, the CME leaders may use different presentation material at their respective CME sessions, which may introduce bias.

A limitation to our study is the use of a nonvalidated questionnaire for the PCPs. However, as our CME has introduced ILOs that have not been included in COPD training before, a validated method of measuring the effects in COPD management and treatment is not currently available. We have tried to enhance our chances of gathering satisfactory data by using diversity in design and analysis of data. The nonvalidated questionnaire together with the lack of previous studies mean that there is no primary endpoint measure to use for power calculation for PCPs. We plan to analyse the nonresponders to the first and second questionnaire.

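### Physician open answers are marked against guidelines the plan expects to change before endline, with no edition fixed, and free-text marking is not protected from knowledge of arm

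*Protocol article*

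**What the plan says.** All references are to the protocol article.

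- **Marking standard.** *Outcome measures for PCPs* states, for the open questions, that "each reply is considered correct only when it is in line with current COPD care guidelines". Free text is scored "yielding 0–2 points according to a correction template, which will be constructed in alignment with the guidelines". No edition or date is attached, and the template is spoken of in the future tense.
- **Other items.** The same section gives 13 questions worth 0–2 points each. Multiple choice items are scored 2, 1 or 0 by a fixed rule and also rest on learning outcomes drawn from current guidelines. How many of the 13 are open is not stated.
- **What is taught.** *Intended learning outcomes (ILOs) of the CME* bases the content on specific cited guidelines and on the problem areas from an earlier interview study. The examination questions are built on the learning outcomes shared by both taught arms.
- **Expected revision.** *Relevant parallel, permitted interventions* says that "new guidelines for COPD care in Sweden are expected to be published during the study period". The *PCPs* part of the Discussion repeats that "the national guidelines are to be revised during the study period" and gives this as the background to having a reference group.
- **Timing.** Physician endline is 1 year after the completed CME (*Recruitment of PCPs and data collection*).
- **Blinding and handling.** *Study design* declares the trial unblinded. *Sequence generation and allocation procedure* has the research group told the arm of each centre. In *Recruitment of PCPs and data collection*, "The completed questionnaires will be collected by the research group". The marker is not named.

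**The concern.** A test used before and after teaching measures learning only if the same reply earns the same mark on both occasions. Here the standard of correctness is described by a word, current, whose content the plan itself expects to change between the two occasions.

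The reference group is the most exposed. It is there to show what general information around the guideline revision does to physicians who receive no CME. If the key changed with the revision, that group's change would contain both the effect of the information and the effect of the new key, and the two could not be separated. The group is also recruited separately rather than randomised, so its calendar dates need not match those of the taught arms.

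The marking of free text is a second, independent matter. A template narrows a marker's discretion but does not remove it. A marker who knows the arm, in a trial with a stated hypothesis in favour of one arm, can lean towards that arm.

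Physician competence is part of the main aim and is the mechanism in the hypothesis (*Objective and hypothesis*). This questionnaire is its only instrument, and the article already acknowledges that it is not validated.

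**Working it through.** There is no stated figure to reproduce: the article gives no power calculation for physicians and no standard deviation for their score. The check is therefore a comparison of readings, plus a little arithmetic on scale.

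**1. Scale.** 13 questions × 2 points = 26 points at most. One question is 2/26 = 7.7% of the range, two are 4/26 = 15.4%, three are 6/26 = 23.1%. These are ceilings for one physician. The number of questions a revision would touch is not in the document.

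**2. Two readings of the marking rule.** Take one question whose right answer the revision reverses (a worst case), and a physician who answers by the old text at baseline.

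| Endline answer | One key, old edition | Key follows current edition |
|---|---|---|
| Old text (retains what was taught) | 2 to 2, change 0 | 2 to 0, change −2 |
| New text (has followed the revision) | 2 to 0, change −2 | 2 to 2, change 0 |

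The two readings reverse which physician appears to lose competence. With a fixed key, a given reply keeps its mark, but up-to-date answers are penalised. With a moving key, an unchanged reply loses marks. Fixing the key removes the instability over time. The penalty on updated answers remains, so a sensitivity analysis is needed as well.

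**3. Does the key alone bias arm 1 against arm 2?** Let p1 and p2 be the shares of physicians in the two arms who answer the reversed question by the old text at endline. Under a revised key the mean losses are 2·p1 and 2·p2, and the arm contrast moves by 2·(p1 − p2). With p1 = p2 the loss cancels. If p1 and p2 differ because one arm retained more of what was taught, that is itself a difference in learning. So the key by itself does not produce a clear spurious difference between the randomised arms. The reference group was not taught the old text and may be assessed at other dates, so no such cancellation can be relied on there.

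**4. Marking by someone who knows the arm (illustration only).** Assumptions not taken from the plan: the 26-point total is compared as a mean, its SD is 3, 4 or 5 points, the test is two-sided at 5%, and the ICC of 0.01 that the plan sets for its sample size also holds for physician scores. From the plan: 60 physicians and 11 centres per arm.

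- Cluster size: 60/11 = 5.45. Design effect: 1 + (5.45 − 1) × 0.01 = 1.045.
- Standard error of the difference: SD × √(2 × 1.045/60) = 0.187 × SD.
- With no true difference, a marking lean of 1 point on the total in one arm gives rejection in about 43%, 27% or 19% of trials for SD 3, 4 or 5. A lean of 0.5 point gives about 15%, 10% or 8%. The nominal rate is 5%.

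This shows only that a small lean would matter. It is not evidence that one will occur.

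**5. Handling of forms.** For patients, *Recruitment of patients and data collection* puts an independent person in charge of the codes. No similar step is described for the physicians' questionnaires.

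**The case against.** **The key is probably meant to be single.** The learning outcomes rest on particular cited guidelines, the examination is built to match those outcomes, and the article speaks of one template. Nothing says that the key will be updated. This is the more natural reading, and it stands. It does not settle the matter, because the rule as written points to current guidelines and the template did not yet exist.

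**Nobody is said to mark unmasked.** A reader might infer that the research group scores the free text knowing the arm. The document does not say so: it declares the trial unblinded, discloses allocation to the group and has the group collect the forms. Masked marking is not excluded, and an article may leave the marker's identity to the full protocol. That much stands. The point rests on what is stated, which leaves free-text scoring unprotected.

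**No bias between the randomised arms.** A reader might infer that a changed key tilts arm 1 against arm 2, for example by supposing that 20% more physicians in one arm answer one question by the old text, so that means differ by 0.20 × 2 = 0.4 points without any difference in competence. The documents do not support this. The 20% has no source, such a gap would itself be a difference in retained teaching, and *Physician data* plans comparisons of proportions and odds ratios, not of mean totals.

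**Limited exposure.** Multiple choice items have fixed scoring, so marker judgement touches only the open questions. Several of those concern matters such as smoking cessation support or attitudes, and the document gives no reason to think a revision would reverse them. This stands, and is why no size can be claimed.

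**The reference group handles the revision.** It addresses what physicians learn from the revision, not which edition marks them.

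**Conclusion.** The point holds in a limited form. The plan ties correctness to a standard it expects to change before endline, fixes no edition, and had not yet written the template. If the key moved, change over time and the contrast with the reference group would not be interpretable as learning. This does not by itself clearly favour either randomised arm.

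The possible bias between arms comes from free-text marking without described masking, in an unblinded trial where the research group knows the allocation. That is an exposure inferred from the stated arrangements, not a stated practice.

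The size cannot be derived from the document. The ceiling is 2 of 26 points per physician for each reversed question, and the rejection rates above depend on an assumed SD, an assumed lean and an assumed comparison of means. Only the physician outcome is affected. The primary outcome, patient-reported CCQ, and the sample size built on it are not. The change is worth making because it is cheap and protects the only measure of physician competence.

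**What to change.** 1. Name the guideline editions behind the learning outcomes as the marking standard. Write one dated correction template from them, lock it before endline replies are read, and apply it to baseline and endline in all three groups, multiple choice key included.
2. Mark the free-text replies in random order from coded copies that hide the centre, the arm and the time point.
3. Add a sensitivity analysis that drops, or re-keys to the revised guidelines, any question whose answer the revision affects, and list those questions.

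Cost: clerical work to copy, code and shuffle at most about 180 × 2 = 360 questionnaires, and one extra scoring run. The design, the sample size and the patient outcomes do not change.
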